## Abstract

**Background:**

Psychological therapies are effective treatments for hypoactive sexual desire dysfunction (HSDD; formerly hypoactive sexual desire disorder), a common sexual dysfunction among women. Access to evidence-based treatments, however, remains difficult. Internet-based interventions are effective for a variety of psychological disorders and may be a promising means to close the treatment gap for HSDD.

**Objective:**

This article describes the treatment protocol and study design of a randomized controlled trial, aiming to study the efficacy of cognitive behavioral and mindfulness-based interventions delivered via the internet for women with HSDD to a waitlist control group. Outcomes are sexual desire (primary) and sexual distress (secondary). Additional variables (eg, depression, mindfulness, rumination) will be assessed as potential moderators or mediators of treatment success.

**Methods:**

A cognitive behavioral and a mindfulness-based self-help intervention for HSDD will be provided online. Overall, 266 women with HSDD will be recruited and assigned either to one of the intervention groups, or to a waitlist control group (2:2:1). Outcome data will be assessed at baseline, at 12 weeks, and at 6 and 12 months after randomization. Intention-to-treat and completer analyses will be conducted.

**Results:**

We expect improvements in sexual desire and sexuality-related distress in both intervention groups compared to the waitlist control. Recruitment has begun in January 2019 and is expected to be completed in August 2021. Results will be published in 2022.

**Conclusions:**

This study aims to contribute to the improvement and dissemination of psychological treatments for women with HSDD and to clarify whether cognitive behavioral and/or mindfulness-based treatments for HSDD are feasible and effective when delivered via the internet.

**Trial Registration:**

ClinicalTrials.gov NCT03780751; https://clinicaltrials.gov/ct2/show/NCT03780751

**International Registered Report Identifier (IRRID):**

DERR1-10.2196/20326

## Introduction

### Background

A sexual dysfunction can be described as a disturbance in a person’s ability to respond sexually or to experience sexual pleasure that leads to significant personal distress [1]. One of the most common sexual dysfunctions among women is a lack of sexual desire which, according to the eleventh edition of the International Classification of Diseases (ICD-11), can manifest as reduced or absent spontaneous desire (sexual thoughts or fantasies), reduced or absent responsive desire to erotic cues and stimulation, or an inability to sustain desire or interest in sexual activity once initiated [2]. If a pattern of low sexual desire is present over a period of at least several months and is associated with clinically significant distress, a hypoactive sexual desire dysfunction (HSDD; formerly hypoactive sexual desire disorder) can be diagnosed. A UK study found that among 6777 sexually active women, 34.2% experienced low desire [3]. When applying the morbidity criteria listed in the fifth edition of the Diagnostic and Statistical Manual of Mental Disorders (DSM-5), 6.5% of women indicated low sexual desire or arousal for several months within the last year, and 0.6.% met the criteria for female sexual interest/arousal disorder [4]. Low sexual desire does not only affect women’s sexual health but also has detrimental effects on their quality of life [5]. Individuals with sexual dysfunctions (including low desire) are more likely to report higher rates of sexually transmitted infections, unwanted sex, unemployment, relationship breakdown, and difficulties discussing sexuality [3]. In addition, low sexual desire is often comorbid to mental health problems such as depression and anxiety [6,7].

### Treatment of Low Sexual Desire

Low sexual desire has received widespread attention from clinicians, researchers, and the lay public because of its high prevalence and its seeming resistance to treatment [8] which led to increased efforts to find a “Pink Viagra” (ie, an effective pharmacological agent) [9]. To date, flibanserin is the only drug that has received approval for treatment of low sexual desire in women in the United States and Canada. While this drug, which has pharmacological effects on serotonin and dopamine receptors [10], was being tested on patients with major depressive disorder, its positive effect on women’s sexual functioning was discovered [11]. So far, 3 systematic reviews or meta-analyses have found modest positive effects on women’s low sexual desire [12-14], while also acknowledging its side effects (eg, nausea, dizziness, fatigue). There has also been renewed interest in the advancement of psychological treatments for women’s low sexual desire [9]. A meta-analysis found psychological interventions to be effective treatments for low sexual desire [15] and effects for symptom reduction were large compared to waitlist controls (*d*=0.91; 95% CI 0.38-1.45; *P*=.012). Furthermore, such treatments lead to medium to large increases in sexual satisfaction.

Among the most common treatments for low desire are cognitive behavioral therapy (CBT) and mindfulness-based therapy (MBT) [15]. CBT is change oriented and is one of the most researched forms of psychotherapy. It is effective for a variety of mental health problems such as depression, anxiety disorders, and posttraumatic stress disorder [18], as well as sexual dysfunctions such as HSDD [15]. MBT is an acceptance-based approach using mindfulness, an ancient Eastern practice with roots in Buddhist meditation, defined as present-moment, nonjudgmental awareness [19], and intends to shift the focus of attention to one’s body and breath. MBT has been found effective for the treatment of depression, anxiety, and stress [20]. Evidence for its effectiveness for women’s sexual dysfunctions stems from a few, mostly uncontrolled, studies [17,21,22].

### Internet-Based Interventions

Although many women are distressed by their lack of desire, the number of those who receive qualified, evidence-based treatment remains low [23]. Sexual dysfunctions are connected to stigma and reluctance in seeking professional help [24,25]. Furthermore, a lack of information on the treatment options prevails as well as structural barriers, such as limited access to qualified therapists. This issue could be addressed by developing and disseminating treatments that require less direct forms of contact, namely internet-based interventions. A growing body of literature suggests that interventions delivered via internet or mobile technology are feasible and effective to improve depression, anxiety [26], and even psychosis [27]. These interventions offer varying degrees of guidance ranging from self-help, user-led interventions, to regular to contact with a trained clinician. Interventions involving at least some kind of guidance or coaching have been proven to be more effective than unguided interventions [28]. Concerning internet-based interventions for sexual dysfunctions in women, van Lankveld [29] reviewed 5 studies and found that these interventions were effective in improving sexual functioning and emotional intimacy in couples. While 2 of these studies also included women with low sexual desire [29], treatments did not focus on improvement of sexual desire but targeted a broad range of women’s sexual difficulties (eg, anorgasmia, genital pain). Thus, no studies have evaluated the efficacy of internet-based CBT (I-CBT) or MBT (I-MBT) designed for the treatment low sexual desire in women.

### Study Aim

The aim of this study is to present the protocol of a randomized controlled trial (RCT) comparing 2 internet-based interventions for low sexual desire in women with HSDD to a waitlist. Hypotheses 1 and 2 are that at posttreatment (12 weeks after randomization), women receiving I-CBT or I-MBT report significantly more sexual desire (primary outcome; H1) and less sexuality-related distress (secondary outcome; H2) compared to a waitlist control condition. It is also proposed that these differences are maintained at the 6- and 12-month follow-up assessments. Differences in outcomes between I-CBT and I-MBT at the 12-week-, 6-month, and 12-month assessments are inspected on an exploratory basis. It is also explored whether improvements from pretreatment to posttreatment are dependent on treatment dosage (eg, completed modules, time spent with at-home exercises) and whether changes in proximal variables such as mindfulness or rumination mediate improvement in symptoms in either one of the treatments. Whether improvements in symptoms are predicted by changes in sexuality-related interpretations and associations assessed with computerized reaction-time paradigms (ie, Single-Target Implicit Association Test [STIAT] and Scrambled Sentences Task [SST]) is examined as well. To explore participants’ perceptions of the treatments more thoroughly, qualitative telephone interviews will be conducted with 25 participants in the I-CBT and I-MBT condition, respectively.

## Methods

### Design

The study is an RCT of 2 internet-based treatments (ie, I-CBT and I-MBT) versus a waitlist control group. Analyses will be conducted and reported in accordance with the statement by Consolidated Standards of Reporting Trials (CONSORT) [30]. Recommendations for the reporting of psychological and eHealth interventions will be considered [31,32]. This 3-arm superiority trial with 2:2:1 allocation ratio will demonstrate whether the benefit from I-CBT or I-MBT is superior to natural remission of low desire symptoms. Outcomes will be assessed at baseline (T1), at midtreatment (T2, 5 weeks after randomization, only in active conditions), at posttreatment (T3, 12 weeks after randomization), and at 6 months (T4) and 12 months (T5) after randomization. Two computerized reaction-time paradigms will be administered at T1 and T3. Participants will receive up to 3 reminders for each assessment (after 7, 14, and 21 days). Qualitative telephone interviews with active participants will be conducted at T3. For an overview of participant flow, see Figure 1.

**Figure 1 figure1:**
[figure not shown]
Participant recruitment flowchart.

### Participants

#### Inclusion and Exclusion Criteria

Inclusion criteria are being 18 years or older; completion of the informed consent form; female gender; being able to read, write, and speak German; and meeting ICD-11 criteria for HSDD. Exclusion criteria are being pregnant, ongoing treatment for any sexual dysfunction or plans to enter such treatment, symptoms of a physical condition that might interfere with study participation (eg, cancer, multiple sclerosis), current substance use disorder, current or lifetime schizophrenia spectrum or other psychotic disorders, and significant relationship discord or violence. As sexual dysfunctions show high rates of comorbidity with other mental health issues such as anxiety or affective disorders [7,33], women experiencing mild to moderate symptoms of other mental disorders are not excluded automatically. Rather, symptoms of a mental disorder (eg, eating disorders, obsessive-compulsive disorder, posttraumatic stress disorder, major depression, bipolar disorder) that might interfere with participation (ie, might make it too burdensome for individuals to participate in data assessments) are assessed during screening. Women whose low desire may be fully attributable to pain during sexual intercourse are also not included. Inclusion and exclusion criteria will be assessed in a 2-step process consisting of an online screening followed by an in-depth telephone interview with a clinical psychologist.

#### Procedure

In order to recruit a diverse sample of women of different ages, sexual orientations, and ethnicities, a variety of recruitment strategies will be employed. Women can learn about the study by visiting a designated study website and associated pages on social networks, articles in local and nationwide media publications (eg, magazines, newspapers), online discussion boards, and flyers at specialized counseling agencies/sites, general practitioners, and gynecologists.

Recruitment and study enrollment will follow a stepwise procedure. Potential participants will be invited to complete an online questionnaire assessing inclusion and exclusion criteria. Individuals not meeting the study criteria (eg, male gender, no sexual concerns, or minors) will be informed and, if needed, be referred to other resources (eg, their physician, counseling services). For all other individuals, an in-depth telephone interview with a clinical psychologist will be scheduled to evaluate eligibility. If an individual is eligible, she will receive an invitation to an internet-based questionnaire. Women who complete this baseline assessment and who provide informed consent electronically will be enrolled.

#### Randomization

Enrolled participants will be randomly assigned to 1 of the 3 conditions. To maximize the power of the study to detect differences between active and control conditions, quotas are applied to allocate 40% of participants to each of the active treatments and 20% to the waitlist. A stratification procedure will be applied to balance relationship status (partner vs no partner) and age (younger than 30 years vs 31 years and older). These variables were selected based on their known effect on sexual desire [34-36]. An internet-based randomization tool will be used by a trained research assistant not involved in the recruitment, screening, or treatment of participants [37]. The clinical psychologist conducting the diagnostic interviews will not be involved in the randomization process but will be informed about the assigned condition after its completion. Block randomization with varying block-sizes will be applied. Participants will be informed about their assigned condition. Participants in the active conditions will gain immediate access to the respective program. Participants assigned to waitlist will receive access to a program of their choice (ie, I-CBT or I-MBT) 6 months after randomization.

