### Power Analysis

Sample size was determined based on an a priori power analysis and practical considerations. Psychological therapies for sexual dysfunctions in women yield large effects for symptom improvement compared to waitlist controls (*d*≈0.9) [15,29]. To use a conservative estimate, a medium effect of *d*=0.6 was expected for both active conditions compared to the waitlist (unpaired *t* test two-sided, α=.025, 1–β=80%, allocation rate 2/1). In addition, a postsample of 81 women for each of the 2 active conditions would yield statistical power of 60%, 71%, and 81% to detect differences of *d*=0.35, 0.40, or 0.45, respectively. Although this study is not sufficiently powered to detect smaller differences in efficacy between I-CBT and I-MBT, it will still provide first estimates that may be useful for future studies. As internet-based interventions commonly suffer from relatively high attrition rates, a 30% loss at postassessment analysis is expected. Based on these considerations, a total of 266 women will be enrolled in the study.

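### The stated age strata for randomisation leave out women aged exactly 30, and the article does not show which cut-off was meant

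*Protocol article*

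**What the plan says.** The protocol article, under Randomization, allocates women 2:2:1 to I-CBT, I-MBT and waitlist within strata. The first factor is given as "A stratification procedure will be applied to balance relationship status (partner vs no partner"), and the second as "age (younger than 30 years vs 31 years and older"). The section explains that both were chosen because they are known to affect sexual desire, which is the primary outcome. It adds that "Block randomization with varying block-sizes will be applied", and that a research assistant with no part in recruitment, screening or treatment operates an internet-based tool.

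On who enters the scheme, the eligibility section states "Inclusion criteria are being 18 years or older" and sets no upper age limit. The Randomization section then says "Enrolled participants will be randomly assigned to 1 of the 3 conditions". No other part of the article gives an age cut-off.

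**The concern.** A stratification factor has to place every eligible participant in exactly one category. The two printed age categories do not meet, because the first ends below 30 and the second begins at 31. Age 30 lies well inside the range of adult women that the trial recruits, so some participants are likely to be affected.

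What is at stake is whether the rule can be carried out and reproduced. From the article alone, a reader cannot say which block sequence supplied the allocation of a 30-year-old. Any tabulation or model by age group would also need a decision about these women that the text does not supply.

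**Working it through.** **Inputs**

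- Age categories: A = age < 30, B = age ≥ 31 (Randomization).
- Eligible ages: 18 and over, with age 30 not excluded (Inclusion and Exclusion Criteria).
- Everyone enrolled is randomised (Randomization).
- Planned enrolment: "a total of 266 women will be enrolled in the study" (Power Analysis).
- Age distribution: not given in the article.

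**Step 1: coverage.** Each whole-year age from 18 to 89 was tested against (age < 30) or (age ≥ 31). The only age that satisfies neither is 30. No age satisfies both, so the categories do not overlap but are not exhaustive. In exact age, the gap runs from the 30th birthday to the day before the 31st.

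**Step 2: possible repairs.** Two single-boundary changes close the gap:

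| Repair | Stratum for a 30-year-old |
|---|---|
| < 30 vs ≥ 30 | older |
| ≤ 30 vs ≥ 31 | younger |

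Under either one, every age from 18 up falls in exactly one category, and the scheme has 2 × 2 = 4 strata with relationship status. The two repairs put 30-year-olds in opposite strata. Nothing in the article favours one over the other.

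**Step 3: how many women.** Because no age distribution is given, this is a range under stated assumptions:

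- Even spread over 18–60: 60 − 18 + 1 = 43 one-year ages. 266 / 43 = 6.2 women, and 1 / 43 = 2.3%.
- Even spread over 20–45: 45 − 20 + 1 = 26 one-year ages. 266 / 26 = 10.2 women, and 1 / 26 = 3.8%.
- Wider bracket of 1% to 5%: 0.01 × 266 = 2.7 and 0.05 × 266 = 13.3, so about 3 to 13 women.

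With 20% allocated to waitlist, the two even-spread cases put about 0.2 × 6.2 = 1.2 and 0.2 × 10.2 = 2.0 of these women in the control arm.

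**Step 4: what depends on the boundary.** The sample size calculation (d = 0.6, two-sided alpha .025, 80% power, 2:1 allocation) does not use the age cut, so no design figure changes. A 30-year-old placed in either stratum is still allocated at random, 2:2:1 within blocks. At most, the balance of the arms on age is slightly affected.

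**The case against.** The strongest reply is that this is a slip in wording and not a failure in conduct. The article does not describe how age enters the randomisation tool. If the tool was set up with a complete cut, every 30-year-old had a defined stratum and nobody had to choose. That is plausible, and nothing in the article contradicts it. It limits the severity but does not remove the error: the article chose to state the rule, and the rule as stated omits an eligible age.

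A reader might go further than the text allows in three ways.

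- *That the research assistant has to choose a stratum and could thereby steer the next allocation.* The article does not support this. A choice arises only if the tool carries the printed categories. Steering would also require knowing the next allocation in both candidate strata. The same section makes the assistant independent of recruitment, screening and treatment, keeps the interviewing psychologist out of the randomisation until it is complete, and varies the block sizes.
- *That the treatment comparison is biased.* It is not, for the reason given in the last step of the check.
- *That a planned analysis is left undefined.* Statistical Analyses names repeated measures ANOVA of each active arm against waitlist and mentions no stratum term. Nothing says that the exploratory moderator models would use age in this dichotomised form. The undefined stratum would matter only where the age group is actually used.

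The article's silence on stratum terms is not counted as an error, since an analysis plan that is not shown may settle it.

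**Conclusion.** The point holds as a minor error in a stated randomisation rule. The printed age categories omit women aged exactly 30, who are eligible and must be randomised, and the article does not show which of the two natural cuts was intended. That conclusion rests on the text alone and needs no assumption.

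The size does rest on an assumption: perhaps 2% to 4% of the 266 women, or about 6 to 10, if ages are spread evenly over the ranges tried above. Whether any of these women was handled inconsistently cannot be known without the tool's settings or the log.

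**What to change.** 1. State the cut actually programmed in the tool as exhaustive categories: either under 30 against 30 and over, or up to and including 30 against 31 and over. This takes one sentence.
2. Check in the randomisation log how women aged 30 who were enrolled since recruitment began in January 2019 were assigned, and report the result. This is a single look-up over a handful of records.
3. Include the stratification factors as randomised (age group and relationship status) as factors in the primary analysis. This adds two terms to the model and needs no new data. It is an inexpensive improvement that brings the analysis into line with the design; the wording gap does not itself require it. Using the strata as randomised also fixes the category of each 30-year-old, so no further analysis on a re-derived age group is needed.

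No change to sample size, allocation ratio or significance level follows.

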### Power Analysis

Sample size was determined based on an a priori power analysis and practical considerations. Psychological therapies for sexual dysfunctions in women yield large effects for symptom improvement compared to waitlist controls (*d*≈0.9) [15,29]. To use a conservative estimate, a medium effect of *d*=0.6 was expected for both active conditions compared to the waitlist (unpaired *t* test two-sided, α=.025, 1–β=80%, allocation rate 2/1). In addition, a postsample of 81 women for each of the 2 active conditions would yield statistical power of 60%, 71%, and 81% to detect differences of *d*=0.35, 0.40, or 0.45, respectively. Although this study is not sufficiently powered to detect smaller differences in efficacy between I-CBT and I-MBT, it will still provide first estimates that may be useful for future studies. As internet-based interventions commonly suffer from relatively high attrition rates, a 30% loss at postassessment analysis is expected. Based on these considerations, a total of 266 women will be enrolled in the study.

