### Limitations

This study is sufficiently powered to allow for a comparison of I-CBT and I-MBT to a waitlist control group for our primary outcome measure (ie, the SIDI-F-SR). Thus, it will not allow us to identify smaller differences in efficacy between the 2 active conditions or subtle changes in other variables. Although efforts have been made to create study content that should be appropriate and helpful for a wide variety of participants (eg, optional content, case vignettes with women of different ages, partnership status, and sexual orientations), not all women may find the interventions suited for their needs. All treatment modules include audiovisual content (eg, infographics, videos, audio files) to supplement text-based information; still, women with reading difficulties or non-German speakers might find study participation difficult. The same problem applies to the data assessments which mostly rely on internet-based self-report questionnaires. Some participants may need up to 50 minutes to complete data assessments which require a high level of commitment and concentration and place an additional burden on participants.

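### The 266 women enrolled do not cover the planned 30% loss: about 74 per active arm remain instead of 81, and power against waitlist is 76%, not 80%

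*Protocol article*

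**What the plan says.** All the figures are in the protocol article.

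- **Target.** Power Analysis assumes that d="0.6 was expected for both active conditions compared to the waitlist", using an unpaired t test specified as "two-sided, α=.025, 1–β=80%, allocation rate 2/1".
- **Sample after loss.** The same section says that "a postsample of 81 women for each of the 2 active conditions would yield statistical power of 60%, 71%, and 81" per cent for differences of 0.35, 0.40 and 0.45 between the active arms. The 81 is therefore explicitly a post-assessment number.
- **Loss and enrolment.** The section ends: "a 30% loss at postassessment analysis is expected. Based on these considerations, a total of 266 women will be enrolled in the study".
- **Allocation.** Randomization states that "quotas are applied to allocate 40% of participants to each of the active treatments and 20% to the waitlist".
- **Claim.** Limitations says: "This study is sufficiently powered to allow for a comparison of I-CBT and I-MBT to a waitlist control group", with reference to the primary outcome measure.

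The article does not print the inflation formula or the required waitlist number. It says that the sample size rested on the power analysis and on practical considerations.

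**The concern.** If a fraction L of those enrolled is lost, the number to enrol is the required number divided by (1 − L). Multiplying by (1 + L) is a common slip. It always enrols too few, and the gap grows with L. At 30% the two factors are 1.30 and 1/0.7 = 1.43.

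The total of 266 looks like the result of that slip. If so, a reader who takes the 30% loss at face value is misled on two counts: the number of women expected with 12-week data, and the power of the primary comparison. The power quoted for the comparison between the two programs rests on the same 81 per arm.

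**Working it through.** **Inputs.** From Power Analysis: d=0.6, two-sided α=.025, 80% power, 2:1 allocation, 81 per active arm at post-assessment, 30% loss, 266 enrolled. From Randomization: 40%/40%/20%.

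**Method.** Noncentral t power, with noncentrality δ = d / √(1/n₁ + 1/n₂) and n₁ + n₂ − 2 degrees of freedom.

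**1. Reproduce the required post-assessment sample.**
- 81 vs 41: δ = 0.6/√(1/81 + 1/41) = 3.13, power 80.4%.
- 81 vs 40: 79.7%. 80 vs 40: 79.5%.

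So 81 active and 41 waitlist is the smallest sample at about 2:1 that reaches 80%, and it matches the article's 81. Three arms need 81 + 81 + 41 = 203 women with post-assessment data.

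**2. Reproduce the active-versus-active power.** With 81 per arm and two-sided α=.05, d=0.35, 0.40 and 0.45 give 60.0%, 71.6% and 81.2%. These agree with the printed figures, so 81 is the number the authors used.

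**3. Reproduce 266.**

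| Inflation | Active, each | Waitlist | Total, rounding up per arm |
|---|---|---|---|
| × 1.3 | 105.3 → 106 | 53.3 → 54 | 266 |
| ÷ 0.7 | 115.7 → 116 | 58.6 → 59 | 291 |

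On the overall total, 203/0.7 = 290. Only the multiplication gives 266.

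**4. Apply the stated loss to 266.**
- Each active arm: 266 × 0.4 × 0.7 = 74.5.
- Waitlist: 266 × 0.2 × 0.7 = 37.2.
- Total: 266 × 0.7 = 186.2, against the 203 required.

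**5. Power with that sample.**

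| Comparison | Printed | 266 enrolled, 30% lost |
|---|---|---|
| Active vs waitlist, d=0.6, α=.025 | 80% | 76.2% (δ = 2.99) |
| I-CBT vs I-MBT, d=0.35, α=.05 | 60% | 56.4% |
| I-CBT vs I-MBT, d=0.40 | 71% | 67.9% |
| I-CBT vs I-MBT, d=0.45 | 81% | 77.9% |

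The effect detectable against waitlist with 80% power is d=0.63.

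**6. Loss that 266 can absorb.** Each active arm starts with 266 × 0.4 = 106.4 women, and 1 − 81/106.4 = 23.9%. For the total, 1 − 203/266 = 23.7%. Power against waitlist is 80.3% at 23.5% loss and 79.98% at 24%. The printed figures therefore hold up to a loss of about 24%.

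**The case against.** - **The multiplication by 1.3 is a reconstruction.** The article prints no formula and mentions practical considerations. This is right, and the step should be described as inferred. But the text does not say that lower power was accepted, and step 4 holds however 266 was obtained.
- **The active-versus-active figures are conditional.** They are correct for 81 per arm, the comparison is exploratory, and the article admits low power for small differences. This stands. The fault is only that the plan does not expect to have 81 per arm.
- **The planned analysis is not a t test on post scores.** Statistical Analyses specifies repeated measures ANOVA, and Primary Outcome reports a test–retest correlation of 0.74 over 14 weeks. As an illustration with 74.5 vs 37.2 women and equal variances at both times, a change-score test has power of 97% if the pre-post correlation is 0.74, 86% at 0.6, 76% at 0.5 and 68% at 0.4. Baseline adjustment reaches 80% from a correlation of about 0.3. So the shortfall does not show that the final analysis will lack power. It does show that the printed calculation, which takes no credit for baseline, does not give the printed result.
- **Multiple imputation keeps all 266 women in the analysis.** It does not in itself restore the missing outcome information, and the section reasons from the post-assessment sample.
- **d=0.6 is conservative against the cited value of about 0.9.** At d=0.9 the reduced sample has about 99% power. This bears on the chance of success, not on whether the calculation is right.

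**Conclusion.** The point holds. An enrolment of 266, a 30% loss and 81 women per active arm cannot all be true. Under the plan's own assumptions (unpaired t test on post-assessment data, equal 30% loss in every arm, 2:2:1 allocation), power against waitlist at d=0.6 is 76%, about 4 points below target. Enrolment is 24 to 25 women short of the 290 to 291 needed. The figures between active arms are each 3 to 4 points too high. The statement of sufficient power in Limitations is not supported on this basis, although a baseline-adjusted analysis might well meet it. The error is one of stated figures and modest in size. It affects no estimate, test or error rate.

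**What to change.** Any one of the following makes the section consistent.

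1. **Keep 266 and restate the figures (preferred).** Suggested wording: 'With 30% loss, about 74, 74 and 37 women are expected at 12 weeks. This gives 76% power at d=0.6 against waitlist (80% at d=0.63), and 56%, 68% and 78% power for I-CBT versus I-MBT at d=0.35, 0.40 and 0.45.'
2. **Keep 266 and change the loss.** State that the sample allows for about 24% loss, with a reason for expecting no more than that.
3. **Enrol about 291.** A 30% loss then leaves about 81.5, 81.5 and 40.7 women, with 80.3% power.

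Under option 1, qualify the Limitations sentence with the achieved power. If the authors want to rely on the baseline measurement to recover the shortfall, they should state the assumed pre-post correlation and base the power on that analysis.

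Options 1 and 2 cost only wording. Under option 1 the stated power becomes slightly less favourable. Option 3 costs about 25 further women.
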